#### Individual Outcomes (RQ5)

We will explore the indications of effectiveness at the individual level through changes in students’ health behaviors and well-being. Items to assess health behavior will primarily consist of validated measures and items used in other national health profile studies in Denmark (Table 2). The research team will preidentify one primary and one secondary outcome indicator item for each targeted health area (ie, dietary behavior, physical activity, alcohol consumption, marijuana and drug use, and well-being). The primary indicator will be an item assessing students’ health behavior during school time, and the secondary indicator will be an item assessing health behavior during leisure time or overall.

Following Bauman and Nutbeam [8], we will assess both health behavior and health promotion outcomes to understand the complexity of health behavior. While health behavior outcomes are expressed in terms of changes in, for example, levels of physical activity or mental well-being, health promotion outcomes are personal, social, and environmental factors that are a means of improving people’s ability to change behavior [8]. Therefore, health promotion outcomes are considered intermediate to health behavior (see Table 2 for examples).

The questionnaire data will be collected 4 times (Figure 2). Regardless of the specific health issue each school chooses to address, all students will receive the same questionnaire to identify potential intended and unintended consequences on other health promotion outcomes or behaviors, as suggested in a complex systems sense [46,72]. Electronic questionnaires in SurveyXact [70] will be distributed during school hours by the research team, who will be present in the classrooms so that students can ask questions as they complete the questionnaire. The estimated student population of the 8 program schools is approximately 2000 and, based on previous experience with this procedure [54], we expect that 90% of the students present in class will complete the questionnaire at each of the 4 data collection points. Informed consent will be obtained from all students and can be withdrawn at any time.

Most analyses will be based on cross-sectional data and descriptive in nature, interpreting the mean differences between the intervention and control groups. However, the analyses will also include linear mixed models with time and selected covariates (eg, gender, age, ethnicity, and socioeconomic status) as fixed effects and school as a random effect. It is important to note that the total time of 2 years to assess individual outcomes may be too short to provide conclusive evidence at this level.

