### The Complexity of Health Behavior

The application of health promotion can strengthen the capability of individuals to take action and build the capacity of groups, communities, or organizations to act collectively to exert control over the determinants of health [8]. The determinants of health are complex and influenced by underlying dynamic factors at multiple levels (ie, individual, intrapersonal, organizational, environmental, neighborhood, and structural) [9,10]. Evidence suggests that chancing organizational structures and processes and strengthening relationships between organizations are more likely to maintain healthy behavior among individuals than programs that target individual behavior change only [11]. In addition, multicomponent approaches (a combination of structures, processes, and individual behavior changes) for health promotion are more effective than single-component programs [12,13].

A challenge for health promotion is the “voltage drop” that has been identified when effective programs are scaled up across contexts (eg, schools of different sizes), as different contexts lead to different outcomes [14,15]. Vocational students’ health behaviors and well-being vary across educational tracks (technical, business, agriculture and food services, social and health services) and regions [7], requiring the use of local data to identify intervention opportunities and priorities. Data-driven programs that use relevant local data to strengthen intervention design are emerging in health promotion research. These programs explicitly consider local conditions as a means of increasing the strength and relevance of the interventions implemented [16,17].

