## Methods

### The Vocational School Setting

Vocational education in Denmark prepares students for specific occupations and is divided into four main educational tracks: (1) technical (eg, electrician), (2) business (eg, office assistant), (3) agriculture and food service (eg, farmer or chef), and (4) social and health service (eg, health care assistant). Vocational education alternates between school-based training and workplace-based training, with approximately one-third of the time spent in school [36]. Some schools are multisited and have student populations greater than 6000, whereas other schools are located at a single address with a student population of no more than 100. Almost two-thirds of students are men (64.7%), but the gender distribution varied according to educational track; for example, the proportion of men is 89.3% in technical education but only 12.3% in social and health service education [37]. The average age of students is 24 years; some students enroll directly from primary school (aged 15-17 years), whereas others begin later in adult life (39.8% is aged >25 years) [37].

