We will examine preliminary effectiveness (see descriptions of organizational outcomes [RQ4] and individual outcomes [RQ5]) at the organizational level (ie, school organizational readiness) and at the individual level (ie, students’ health behavior and well-being) using a quasi-experimental design with a nonrandomized clustered stepped-wedge strategy. The 8 program schools will be enrolled in 2 steps, matched by educational track (one school from each main track) and geographic location (2 schools from 2 Danish regions). The matched clusters will be assigned to early start (January 2022) or late start (6 months later). This design allows for a sequential roll-out of the program and allows us to control for differences between study sites (vertical control) and secular trends (horizontal control) during the study period [49]. Organizational- and individual-level data will be collected simultaneously at all 8 schools 4 times during the 2-year study period at baseline and at 3 follow-up points (T1, T2, and T3; Figure 2). As systems change takes time to diffuse into individual behavior changes [31], the research team will in due course seek opportunities and funding for longer-term data collection (ie, a 5- and 10-year follow-up).

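### Most of the RQ5 reading rests on cross-sectional mean differences between nonrandomized schools, with no stated use of the baseline wave or the track matching, and the accompanying mixed model names no intervention term

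*Protocol article*

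**What the plan says.** The protocol article, Individual Outcomes (RQ5), describes the student analysis in two sentences. The first is: "Most analyses will be based on cross-sectional data and descriptive in nature, interpreting the mean differences between the intervention and control groups". The second adds that "the analyses will also include linear mixed models with time and selected covariates (eg, gender, age, ethnicity, and socioeconomic status) as fixed effects and school" entering as a random effect. No intervention or exposure term, track, region or matched pair is named.

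Under Study Design, preliminary effectiveness is to be examined "using a quasi-experimental design with a nonrandomized clustered stepped-wedge strategy". The eight schools are "matched by educational track (one school from each main track) and geographic location (2 schools from 2 Danish regions"), and "The matched clusters will be assigned to early start (January 2022) or late start (6 months later"). All eight are surveyed at baseline and at three follow-ups. The design, it is said, "allows us to control for differences between study sites (vertical control) and secular trends (horizontal control) during the study period".

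Two background statements bear on this. Under The Complexity of Health Behavior, students' "health behaviors and well-being vary across educational tracks" and regions. Under The Vocational School Setting, "the proportion of men is 89.3% in technical education but only 12.3% in social and health service education".

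**The concern.** Study Design claims control of site differences and secular trends, and Individual Outcomes (RQ5) frames its aim as change in students' behavior and well-being. A difference in means between early and late schools at a follow-up wave delivers neither by itself. It carries any difference that was there before the program, because allocation was not random. If students are pooled, the larger schools also set the track mix of each group, and the matching on track no longer balances the comparison.

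The only intervention-control contrast that the article states for RQ5 is this one. The mixed model could do better, but as described it has no term that would estimate a program effect. Late schools also stop being controls about six months in, so a fixed two-group label does not describe exposure at later waves.

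The results are meant to inform whether national scale-up can be recommended, so descriptive differences will be read as indications of effect.

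**Working it through.** The article gives no power, intraclass correlation (ICC), standard deviation or individual school sizes for RQ5, so there is no figure of its own to reproduce. The check uses cluster-level variances in SD units.

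**Inputs from the article.** About 2000 students in 8 schools, 4 starting early and 4 late; 90% of those present in class respond. Taking equal schools, m = 2000 × 0.9 / 8 = 225 per school and wave. This is an upper bound, since the 90% applies only to students present.

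**Assumed.** ICC 0.01 to 0.10; autocorrelation of the school effect between waves (CAC) 0.5 to 0.9.

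**Formulas.** Variance of a school mean: v = ICC + (1 − ICC)/m. Correlation of a school's means at two waves: r = ICC × CAC / v.
- Raw single-wave difference: SE = √(2v/4)
- Adjusted for the school's baseline mean: SE = √(2v(1 − r²)/4)
- Simple change from baseline: SE = √((2/4) × 2v(1 − r))

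Example, ICC 0.05 and CAC 0.8: v = 0.05 + 0.95/225 = 0.0542; r = 0.04/0.0542 = 0.74. Raw SE 0.165, baseline-adjusted 0.111, change score 0.119.

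| ICC | Raw SE | Baseline-adjusted SE, CAC 0.5 / 0.8 / 0.9 | Change-score SE, CAC 0.5 / 0.8 / 0.9 |
|---|---|---|---|
| 0.01 | 0.085 | 0.080 / 0.071 / 0.066 | 0.097 / 0.080 / 0.073 |
| 0.03 | 0.131 | 0.118 / 0.094 / 0.081 | 0.139 / 0.102 / 0.086 |
| 0.05 | 0.165 | 0.146 / 0.111 / 0.092 | 0.171 / 0.119 / 0.096 |
| 0.10 | 0.228 | 0.200 / 0.146 / 0.114 | 0.232 / 0.155 / 0.118 |

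Baseline adjustment gives 0.50 to 0.94 of the raw SE. The change score gives 0.52 to 1.14 and is worse than raw throughout at CAC 0.5.

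**Degrees of freedom.** Eight school means in two groups leave 6 df (t = 2.45), one baseline covariate leaves 5 (t = 2.57), and four paired differences leave 3 (t = 3.18). At ICC 0.05 and CAC 0.8 the 95% half-widths are:
- raw: 0.165 × 2.45 = 0.40
- baseline-adjusted: 0.111 × 2.57 = 0.29
- paired change: 0.119 × 3.18 = 0.38

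At the weakest corner (ICC 0.01, CAC 0.5) baseline adjustment gains almost nothing: 0.080 × 2.57 = 0.206 against 0.085 × 2.45 = 0.208. The formula also treats the regression slope as known; estimating it from eight schools costs a little more.

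**Track and gender mix.** Technical education has 89.3% men and social and health service 12.3%; the other two tracks are assumed to have 50%. Order of sizes: technical, social and health, two others.
- Equal sizes, 225 each: 50.4% men in both groups, no imbalance.
- Early 300/150/225/225, late 150/300/225/225: 56.8% against 44.0%. The gap is 150 × (0.893 − 0.123)/900 = 12.8 points.
- Early 400/100/200/200, late 100/400/200/200: 63.3% against 37.6%. The gap is 300 × 0.770/900 = 25.7 points.

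The unequal sizes are illustrations. For an outcome with an assumed 20-point gender gap, the spurious differences would be 0.128 × 20 = 2.6 and 0.257 × 20 = 5.1 points in an unadjusted pooled comparison.

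**The case against.** The article calls RQ5 preliminary and says two years may be too short for conclusive evidence at this level. Its word cross-sectional can be read as describing the sampling, that is, repeated cross-sections, and not a single-wave contrast; Table 2 lists baseline and changes for the student outcomes. The sentence straight after the contested one brings in mixed models with time, school and student covariates. Gender is the first covariate named and the list is only of examples. A condensed article may leave the full covariate set to an analysis plan.

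Much of this stands. A reader might infer that the baseline is ignored altogether and the matching wasted. The documents do not support that: a model over four waves with a school effect can use the baseline wave, and matching balances track by design when schools are of similar size. A reader might also infer a sizeable confounding bias, for instance a 30-point shift in track shares giving 0.30 × 77.0 = 23 points in the share of men and 4.6 points on an outcome with a 20-point gender gap. That needs something close to the 4:1 against 1:4 size reversal above. The eight schools' sizes are not given, and the wide range under The Vocational School Setting describes Danish vocational schools in general. The planned gender covariate would also address this route.

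What does not fall is the core. The article affirmatively puts most of the RQ5 reading on intervention-control mean differences, states no baseline or matching adjustment for them, and gives the model no term for the program effect. The label preliminary does not make a pre-existing school difference harmless when the results feed a scale-up decision.

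**Conclusion.** The point holds in a limited form. As described, most of the RQ5 reading is open to pre-existing school differences and, only if school sizes or response are unequal, to track and gender mix. It does not deliver the site-difference control claimed under Study Design or the focus on change in RQ5. No bias is demonstrated.

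Using the baseline school mean as a covariate would bring the standard error to about 0.50 to 0.94 of the raw one, under assumed ICC 0.01 to 0.10, CAC 0.5 to 0.9 and 225 students in every school. After the lost degree of freedom the gain runs from almost none to large.

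One might infer a firm 28% gain from subtracting baseline (0.119 against 0.165). That figure belongs to ICC 0.05 and CAC 0.8. With a strictly paired analysis it shrinks to an interval about 6% narrower (0.38 against 0.40), and at CAC 0.5 subtraction loses precision.

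**What to change.** In Individual Outcomes (RQ5), make the main contrast a comparison that uses the baseline wave: the linear mixed model over all waves, with a time-varying intervention-exposure term, time as a fixed effect, school as a random effect, and the student covariates already listed.

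As an alternative, at waves where the late-start schools are still unexposed, use the early-versus-late difference in school means, adjusted for each school's baseline mean, with schools weighted equally across the four track pairs. This must be confined to those waves; once both groups have started, early minus late is no longer an intervention-control difference.

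Keep the unadjusted mean differences as descriptive background, each shown beside the corresponding baseline difference. A strictly paired analysis (3 df) and a model with track and region fixed effects should be sensitivity analyses, because eight schools leave few degrees of freedom.

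The cost is rewording and a little analysis work; baseline, track and region are already available. The change does not remove the design's limits: the comparison with unexposed schools covers only about six months, and confounding by school differences that change over time remains possible.

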### Ethical Considerations

The study has been referred to the Capital Region of Denmark’s legal center for personal data handling (journal number: P-2021-327). The study will be conducted without approval from the Committees on Health Research Ethics for the Capital Region of Denmark (journal number: 22012766), as this is not required for social health science in Denmark [73]. Participation in research related to the study is voluntary and requires written informed consent from all participants. Consent may be withdrawn at any time. Questionnaire data, key files, audio files, and transcripts of interviews and observations will be stored in a secure folder on the corporate network in accordance with the requirements of the Capital Region of Denmark and European General Data Protection Regulation. Only the principal investigator and those with permission from the principal investigator will have access to data. None of the authors have any financial or competing interests.

## Results

This study was launched in 2021, and data collection is expected to be completed in June 2024. The first results will be submitted for publication in January 2024. The results of this research will be disseminated through national and international conferences, peer-reviewed journals, reports, and web-based sources. In addition, key findings will be disseminated through the CoP and other national practice network meetings with stakeholders and policy representatives.

## Discussion

### Overview

The Data Health study is the first to apply a systems approach to the implementation and evaluation of health promotion programs among vocational school students. The program comprises 5 steps aimed at establishing strong collaborations, building local capacity, identifying leverage points, and generating and implementing collective actions for systems change to improve health and well-being among vocational students. The program will be accompanied by a systems-based evaluation to support the sustainability of program implementation and to determine the scalability of the program. Guided by the Medical Research Council guidance, the evaluation will assess implementation outcomes, contextual differences, and the mechanisms through which the program leads to changes in systems, school organizational readiness, and health behavior and well-being.

### Strengths and Limitations

#### Program Implementation

The steps of the Data Health program are based on systems and health promotion theory, previous health promotion evidence, and formative evaluation at a pilot site. This study has the potential to improve the health behavior and well-being of vocational students and reduce social inequalities in health. The use of systems approaches in communities to address childhood obesity has shown promising results [31,74]. However, adaptation to disadvantaged educational settings may be challenging. One possible challenge is to engage students who are only in school for short periods between workplace-based training. As workplaces are likely to be located across municipalities, it may be difficult to engage students in the GMB process and implementation of actions during workplace training. If possible, we will try to involve the local workplaces in creating collective actions in GMB3 to involve the students, even if they are not physically at the school.

In most health promotion programs, resources often run out before the desired changes in individuals or systems are normalized [75]. The sustainability of actions for system change has been demonstrated in communities, with actions continuing to be implemented years after the reduction in research support [76]. On the basis of locally relevant data and existing capacities and resources, we will test whether the program steps can be successfully sustained. However, sustainable and long-term partnerships between schools, communities, and municipalities can be challenging owing to organizational changes or staff turnover. To address this issue, we will seek to engage and motivate commitment at the management level. In addition, the CoP will serve as an informal capacity building and will expectantly keep the organization as the drivers for systems change. If the steps in the program prove to be sustainable and effective, the CoP can be used to disseminate knowledge about methods and approaches to other schools and municipalities interested in implementing the Data Health program.

#### Program Evaluation

This study involves a complex program evaluation. The processes and steps within the Data Health program are systematic but flexible in the sense that the study sites themselves choose the targeted health issue, actions, and process for normalization. The complexity of a systems approach does not allow for a fully randomized controlled trial with a single set of quantitative outcomes [26]. Therefore, we will use a systems-based and quasi-experimental design to test the preliminary effectiveness of the program at an individual and organizational level. We will use mixed methods to account for the complexity and contextual variation. The comprehensive evaluation design of program implementation and outcomes—combining many data sources from different perspectives—will generate new knowledge that can be used in similar or different contexts at the national and international levels.

To our knowledge, few studies have reported on the implementation of systems approaches and sustainment of actions over time [43,77], particularly using GMB as a participatory method. Understanding the use of GMB in a school setting will provide important information for researchers and practitioners regarding enablers and barriers to this approach.

The systems-based evaluation design provides an opportunity to test new system-level evaluation methodologies, such as the Action Scale Model [27], measuring change within complex adaptive systems. There are many uncertainties in studying changes in complex systems, as complex systems are dynamic [26]. Therefore, we recognize that capturing systems change might not be fully comprehensive. To accommodate this, we set systems boundaries to determine what is relevant to capture and will be used to guide the evaluation.

In parallel, we will assess preliminary indications on individual-level outcomes, assessing the effectiveness on students’ health behavior and well-being because of systems change. A limitation of this study is that most of the student data will be cross-sectional because of the vocational school structure. The research team will explore the possibility of tracking individuals’ educational attainment, employment status, and health registers (compiled by Statistics Denmark [78]) 5 or 10 years postprogram implementation.

This study will test a systems change approach in vocational schools and whether such an approach is suitable for adaptation and scale-up. If this study is shown to be sustainable and effective, the established CoP will support implementation at scale.

## Appendix

Multimedia Appendix 1 The Data Health program theory.

## Abbreviations

CLD: causal loop diagram
CoP: community of practice
GMB: Group Model Building
HPS: health promoting school
NCD: noncommunicable disease
RQ: research question
